
#### 2.1.6 *Sample size determination.*

The sample size is set at 37 using the following rationale: the null hypothesis is p = 0.8 and the alternative hypothesis is p > 0.8 for the statistical analysis of the lateralization diagnosis of EP-01 to intracranial electrode insertion concordance ratio. The hypothesis will be tested using an exact one-tailed test of binomial proportions. Assuming an expected percentage agreement of 0.97, a significance level of 0.025, and a power of 90%, the required number of cases is 34. Considering a 10% dropout rate, the target number of cases will be increased to 37.

#### 2.1.7 *Target study population.*

This trial aims to test the efficacy and safety of the EP-01 in patients with intractable epilepsy. Enrolled patients deemed “EP-01 EEG test-initiated participants” are those who are enrolled in the study and begin EEG testing with the EP-01. “EP-01 EEG test-completed participants” are those who complete both the test AND the extended study period. “Discontinued participants” are those who discontinue during the EEG test period or post-observation period for any reason. Cases that have undergone partial resection and have completed the evaluation at 1 year after resection are defined as “epileptic seizure outcome evaluation completed” and cases that are discontinued before the evaluation of the first year after completion of the study period are defined as “discontinued cases during the epileptic seizure outcome evaluation period”. Patients who fail to enroll after consent is obtained are referred to as “ineligible cases,” and patients who fail to start EEG testing with the EP-01 for any reason after enrollment are defined as “dropout cases”.

Enrollment will be primarily based on pre-trial medical evaluations and the requirements of the insertion procedure. Essentially, patients diagnosed with focal-onset seizures (based on clinical and MRI findings, and scalp electrode results) and a vascular anatomy that allows the EP-01 to be guided to a vessel close to the epileptic focus (such as the cavernous sinus, transverse sinus, superior sagittal sinus, or inferior petrosal sinus) are considered eligible for EP-01 and intracranial electrode implantation. For safety reasons, these patients must have a vascular anatomy that allows the EP-01 to be guided to a vessel close to the epileptic focus, such as the cavernous sinus or inferior petrosal sinus. In consideration of the treatment burden on the participant, the examination associated with the decision to implant these EP-01s may be determined based on data obtained up to 90 days prior to obtaining consent.

### 2.2 Data collection, management, and analysis

#### 2.2.1 *Participant backgrounds.*

After obtaining consent, between 30 days and 1 day prior to the insertion of EP-01 electrode study device, the following items will be investigated at the time of registration, after confirming that the selection criteria have been met and that no exclusion criteria are violated. Participant identification codes and background information will be included in the case report form.

(1)Observables: Sex, age, blood pressure, pulse, current medical history (epilepsy classification, seizure-type classification, duration of epilepsy, etiology), complications, other medical history, previous treatment, smoking history, and alcohol consumption history(2)Complications: Diseases that are complicating factors at the time of obtaining consent(3)History: Diseases that occurred before consent was obtained, plus information up to 90 days prior to the date on which consent was obtained, should be investigated. However, the investigator or sub-investigator will not ask the patient to specify the period of any important illnesses such as perinatal anomalies, febrile convulsions, head trauma, psychiatric disorders, malignant tumors, etc.(4)Previous treatments: The history of treatment (including surgical procedures) for the primary disease prior to the time of enrollment.

#### 2.2.2 *Participant pre-insertion examination information.*

To be performed 30 days to 1 day prior to the implantation of the study device. However, if the examination is performed within 90 days prior to obtaining consent, the examination is not required and the data from prior to obtaining consent should be used.

(1)Height and Weight(2)Cervical Echocardiography(3)Blood Tests: Platelet count, activated partial thromboplastin time (APTT), prothrombin time-international normalized ratio (PT-INR)(4)Non-Invasive Tests: Defined as a neuropsychological examination (presence or absence of dysfunction of the left and right frontal, temporal, occipital, and parietal lobes) and an epilepsy interview. According to guidelines, the interview will be conducted to gather information on seizure frequency, seizure status, and triggers, symptoms before and during seizures, persistence of symptoms, symptoms following seizures, presence of trauma, tongue bite, urinary incontinence, post-seizure headache and post-seizure muscle pain, age at first seizure, change and transition of seizures and seizure type, last seizure, seizure and arousal relationship to sleep, post-ictal behavior, and any other pertinent details of the condition(5)MRI and Imaging: MRI and other imaging data (including CT, ^18^F-fluorodeoxyglucose PET, ^123^I-iomazenil-SPECT, magnetoencephalogram, etc., if performed in the usual practice) for lateralization diagnosis of the epileptic focus should be obtained. Obtaining images from the same modalities that were conducted within 1 year prior to obtaining consent will be preferable, but re-imaging for study purposes will not be required(6)Scalp Electrode Testing: Scalp electrode examination data for the lateralization diagnosis of the epileptic focus should be obtained. Testing in the same manner conducted within 1 year prior to obtaining consent will be preferable, but re-testing for study purposes will not be required(7)MRI for Anatomical Evaluation: Simple 3D T1-weighted imaging (3D-T1WI), MR venography, or contrast-enhanced 3D-T1WI should be performed to confirm that the patient has vascular anatomy that allows the main body of the EP-01 to be guided to vessels close to the epileptic focus, such as the cavernous sinus, transverse sinus, superior sagittal sinus, or inferior petrosal sinus. If such imaging has been previously performed within 90 days prior to obtaining consent, no re-imaging will be required and the data should be collected prior to obtaining consent.

#### 2.2.3 *Follow-up.*

The EP-01 main unit is to stay implanted for up to 2 weeks (plus up to 3 days allowance) and then be removed. Intracranial electrodes will be removed according to clinical judgment and may be removed at the same time as the EP-01 unit. A follow-up period of 1 year will be conducted to evaluate the seizure-free rate after focal resection using data obtained from the EP-01 unit.

#### 2.2.4 *Statistical methods.*

The percentage agreement between the lateralization diagnosis of the epileptic focus by EP-01 or intracranial electrodes, plus the 95% confidence interval of the percentage agreement by the Clopper–Pearson method will be determined. Full Analysis Set will be the primary dataset for this analysis.

Regarding missing data, cases where measurements are successfully obtained using intracranial electrodes but not with EP-01 will be considered as discrepancies. If both the intracranial electrodes and EP-01 cannot be measured, the case will be excluded from analysis. If only one of them is measurable, it will be conservatively considered as discordant. With respect to potential confounders, since both devices will be used for all participants, we do not anticipate any confounding concerns. Therefore, baseline characteristics will not be incorporated into the primary analysis. However, if necessary, secondary analyses that account for baseline characteristics will be conducted. As for multiple comparisons, we consider this issue irrelevant as there is only one primary outcome measure. Comparisons for secondary outcomes will also include the calculation of a 95% confidence interval using the Clopper-Pearson method, similar to the primary outcome.

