**Fig 1 pone.0332387.g001:**
[figure not shown]
Study schedule of EPSILON IE. Essentially, the screening period is set at 30 days and the investigational testing period after insertion is a maximum of 2 weeks to facilitate testing and provide sufficient time for non-provoked spontaneous seizures to occur. The post-observation period (1 week) is judged as sufficient for monitoring potential adverse events associated with endovascular and intracranial implantation of electrodes. *Not required if epileptic seizures occur within one week of placement of the test device. ** EP-01 will be left in place until the onset of epileptic seizures or for a maximum of 14 days (plus 3 days). ***If the trial is to be stopped during the clinical trial inspection period, the tests specified at the time of removal of the EP-01 will be carried out as much as possible depending on the subject’s condition, the EP-01 will be removed, and the trial will move to the post-observation period. Suppose the trial is to be stopped during the post-observation period. In that case, the tests specified one week after removal of the test device will be carried out as much as possible depending on the subject’s condition, and the trial will then end. **** Only subjects who underwent epilepsy resection were included. ***** If the measurement is conducted within 90 days before obtaining consent, there is no need to remeasure, and data from before consent was obtained will be collected. ****** When only EP-01 or both EP-01 and intracranial electrodes are indwelled, EEG data from EP-01 and intracranial electrodes will be recorded under video surveillance. EEG data during eyes opening and closing (the investigator, etc. will decide the timing of EEG data acquisition during eyes opening and closing) and EEG data during epileptic seizures will be submitted to the Central Evaluation Committee.

This protocol has been described in accordance with the SPRIT checklist (Standard Protocol Items: Recommendations for Interventional Trials [11].

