To prevent thrombosis of the sheath during implantation of the EP-01 body, continuous perfusion of heparinized saline solution should be performed through the side port of the Tuohy Borst valve attached to the sheath as a rule. If the investigator determines that continuous irrigation with heparinized saline is difficult due to the condition of the subject, flush and lock will be performed at least once a day (heparinized saline is recommended for flushing and locking). During the period of EP-01 implantation, the position of the tip electrode should be confirmed by X-ray examination, and if the position of the tip electrode is found to be significantly misaligned, the safety of the subject will be given highest priority. In addition, the presence or absence of adverse events will be confirmed by CT. If adverse events are confirmed, appropriate treatments will be administered based on the judgment of the investigator.

Note that, because of the complex nature of the study, any therapy that, in the clinical judgment of the investigator or other associated care providers, is necessary for the benefit of the subject may be administered.

Prescribed drugs and therapies used from enrollment to the end of the post-observation period will be noted in the case report as concomitant medications and therapies. Concomitant medications and therapies used for intracranial electrode implantation (including additional implantation) and removal will not be recorded. If focal resection surgery is performed before the end of the post-observation period, concomitant medications and concomitant therapies used for these procedures are also excluded from recording. Antithrombotic therapy, however, will be documented in the case report as antithrombotic therapy from 30 days prior to obtaining consent until the end of the post-observation period.

The placement of intracranial electrodes (such as SDE or SEEG) will follow the insertion of EP-01s, but during the placement of intracranial electrodes, monopolar cautery is prohibited to minimize electrical interference, and head MRI is also not allowed after placement of EP-01s and intracranial electrodes.

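### The both-missing exclusion ignores cause, so a patient whose EP-01 is withdrawn for a device reason before the first seizure may leave the primary analysis instead of counting as discordant

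*Protocol article*

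**What the plan says.** Section 2.2.4 has two rules for missing recordings. If only one device yields a measurement, the case is discordant; this covers a patient with an intracranial recording and none from EP-01. For the other situation it says: "If both the intracranial electrodes and EP-01 cannot be measured, the case will be excluded from analysis". No reason for the missing recordings is asked for.

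Other parts of the protocol article determine who can fall under the second rule:

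- Section 2.1.4 analyses the first seizure after implantation, and section 2.1.5 bases the intracranial determination on ictal EEG. Without a recorded seizure there is no pair.
- The Fig 1 legend leaves EP-01 in until a seizure or for at most 14 days (plus 3). If the trial is stopped in that period, "the EP-01 will be removed, and the trial will move to the post-observation period".
- The same legend describes recording this way: "When only EP-01 or both EP-01 and intracranial electrodes are indwelled, EEG data from EP-01 and intracranial electrodes will be recorded under video surveillance". A period with intracranial electrodes alone is not listed.
- Section 2.2.3 leaves removal of the intracranial electrodes to clinical judgment and permits, but does not require, removal together with EP-01.
- Section 2.1.3 foresees displacement: "if the position of the tip electrode is found to be significantly misaligned, the safety of the subject will be given highest priority". It does not say that the device is then withdrawn.
- Section 2.1.7 reserves the dropout label for patients who never start EP-01 EEG testing. A patient whose EP-01 is withdrawn after testing began is a discontinued participant.

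Section 2.1.6 sets the test: "the null hypothesis is p = 0.8 and the alternative hypothesis is p > 0.8", and "The hypothesis will be tested using an exact one-tailed test of binomial proportions".

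**The concern.** Take two patients in whom EP-01 fails. In the first it stays in place without a usable signal while the intracranial electrodes record the seizure; section 2.2.4 scores this discordant. In the second it has to be withdrawn, for example after an adverse event, before any seizure. If no intracranial seizure is then recorded and used, the patient leaves the denominator. The failure that ended the test can thus cost the device less than the one that did not.

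The same device failure can also be scored either way, depending on when the intracranial electrodes come out and on whether a recording made after EP-01 removal feeds the primary endpoint. The article states no rule on the second point.

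Where such exclusions occur, the primary result moves from the rate at which EP-01 delivers a concordant side towards agreement among patients in whom EP-01 lasted until a seizure. Excluding a case that would otherwise be discordant can only favour the device.

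**Working it through.** **Inputs from section 2.1.6.** "Assuming an expected percentage agreement of 0.97, a significance level of 0.025, and a power of 90%, the required number of cases is 34". The plan then allows for 10% dropout and arrives at a target of 37. The null value is 0.80 and the test is exact and one-sided.

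**Step 1: reproduce the plan's figure.** The pass mark r(n) is the smallest r with P(X ≥ r | n, 0.80) ≤ 0.025. For n = 34, r = 32, with exact alpha 0.0226 and power P(X ≥ 32 | 34, 0.97) = 0.919. No smaller n reaches 0.90 (n = 33 gives 0.740). The stated 34 reproduces. For dropout, 34/0.9 = 37.8; the plan uses 37, and so do I.

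**Step 2: how many discordances are tolerated.**

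| n | Pass mark | Exact p at the mark | Discordances allowed |
|---|---|---|---|
| 34 | 32 | 0.0226 | 2 |
| 35 | 33 | 0.0190 | 2 |
| 36 | 34 | 0.0160 | 2 |
| 37 | 35 | 0.0135 | 2 |

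**Step 3: the same patients, scored both ways.** 37 patients start, and k of them lose EP-01 for a device reason with no usable seizure on either device. Lower limits are Clopper–Pearson, two-sided 95%.

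| k | Excluded | Counted as discordant |
|---|---|---|
| 1 | 34/36 = 94.4%, p = 0.016, limit 0.813: pass | 34/37 = 91.9%, p = 0.045, limit 0.781: fail |
| 2 | 33/35 = 94.3%, p = 0.019, limit 0.808: pass | 33/37 = 89.2%, p = 0.112, limit 0.746: fail |
| 3 | 32/34 = 94.1%, p = 0.023, limit 0.803: pass | 32/37 = 86.5%, p = 0.222, limit 0.712: fail |

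These rows are borderline, with two ordinary discordances each. With k = 3 and perfect agreement otherwise, 34/34 passes (p = 0.0005) and 34/37 fails.

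**Step 4: chance of passing under the current rule.** Two quantities are needed that the article does not give, so both are assumptions:

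- d: the probability that EP-01 is withdrawn for a device reason before the first seizure;
- q: the share of those patients who later give a usable intracranial seizure, and so are discordant under the one-device rule.

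The probability of exclusion is e = d(1 − q). Agreement among those analysed is π = 0.97(1 − d)/(1 − e). With K ~ Bin(37, e),

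P(pass) = Σₖ P(K = k) · P(X ≥ r(37 − k) | 37 − k, π).

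Example: d = 0.05 and q = 0.5 give e = 0.025 and π = 0.97 × 0.95/0.975 = 0.945.

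| d | Expected withdrawals (37d) | q = 0 | q = 0.5 | q = 0.8 | q = 1 (all counted) |
|---|---|---|---|---|---|
| 0% | 0 | 0.90 | 0.90 | 0.90 | 0.90 |
| 5% | 1.85 | 0.89 | 0.68 | 0.53 | 0.44 |
| 10% | 3.7 | 0.83 | 0.42 | 0.23 | 0.13 |

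**Step 5: false passes in the extreme case.** Set q = 0 and let the true rate, with withdrawals counted as failures, be exactly 0.80, so that agreement among those analysed is 0.80/(1 − d). The chance of passing is then 0.013 at d = 0, 0.036 at 3%, 0.062 at 5% and 0.178 at 10%, against the nominal 0.025. Any q above 0 reduces these figures.

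**The case against.** A reader might infer that every early withdrawal of EP-01 leaves both devices without a seizure and so is always excluded. The documents do not support that. Section 2.2.3 lets the intracranial electrodes stay in after EP-01 is removed. If they then record a seizure and the record is used, section 2.2.4 already scores the case discordant. The Fig 1 legend does not list an intracranial-only recording period, but it does not say that such recordings are uncollected or unusable. A figure legend in a condensed article is thin ground for a prohibition. Migration or malfunction with EP-01 left in place is also already penalised when the intracranial electrodes capture the seizure. The q = 0 column is therefore one end of a range and should not be quoted alone.

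The endpoint can also be defended as written. Section 2.1.5 defines agreement between two diagnoses, which requires both to exist. Implantation success, migration, adverse events and device failures are reported separately under section 2.1.5 (secondary endpoints 8 to 10), so these failures are not hidden. Scoring a patient with no reference diagnosis as discordant moves the endpoint towards delivery success, which is a choice.

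These arguments narrow the point and lower its severity. They do not remove it. The exclusion is stated without exception, withdrawal together with the intracranial electrodes is expressly permitted, and the status of later intracranial recordings is left open. Section 2.2.4 itself calls its one-device rule conservative. Excluding a device-caused missing pair runs against that intent.

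**Conclusion.** The concern holds in a limited form. The exclusion in section 2.2.4 is blind to cause, so a device-related withdrawal before the first seizure may drop out of the primary analysis rather than count against EP-01. It does so only if the intracranial electrodes are also removed, record no later seizure, or have their later record left unused.

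The direction is certain relative to scoring the case discordant: the agreement rate can only rise. The size is not known. With only two discordances tolerated at n = 34 to 37, a single such case is enough to turn a fail into a pass. The wider effect rests on the assumed d and q: a chance of passing between 0.44 and 0.89 at d = 5%, and between 0.13 and 0.83 at d = 10%, with 0.97 agreement in all other patients and 37 started. If d is near zero the issue has no practical effect. Severity: should be fixed before the data are analysed.

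**What to change.** Amend section 2.2.4 in three respects:

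1. State that an intracranial seizure recorded after EP-01 has been removed counts as an intracranial measurement without an EP-01 measurement, and is therefore discordant. Align the Fig 1 legend with this.
2. Score as discordant in the primary analysis any both-missing case that follows a device-related withdrawal of EP-01: an adverse event attributed to EP-01, migration, loss of signal or malfunction, as recorded on the case report form. If the sponsor prefers to keep the paired-diagnosis endpoint, apply this scoring at minimum in a prespecified sensitivity analysis reported beside the primary result.
3. Keep the exclusion only for patients with no seizure within the permitted dwell, or who stop for reasons unrelated to EP-01.

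The change concerns the analysis only and touches no clinical decision. It costs a few sentences and a reliable reason-for-removal field. The downside is that the agreement rate may be slightly less favourable and, if device-related withdrawals are not rare, 37 patients give less than the planned 90% power (the q = 1 column above).

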### 2.3 Monitoring

#### 2.3.1 *Data monitoring.*

The analysis of EEG data and device-related adverse events in this trial will be evaluated impartially by an independent review committee. The efficacy evaluation committee comprises four epilepsy specialists. Two will evaluate the EP-01 EEG, and two will assess intracranial EEG, ensuring the study remains blinded. The safety evaluation committee consists of three specialists: an epilepsy specialist, an endovascular neurosurgeon, and a radiation oncologist. Each will evaluate device-related adverse events from the perspective of their respective fields. None of the committee members have any conflicts of interest with the sponsor company.

#### 2.3.2 *Interim analysis and monitoring.*

Because of the relatively short duration of the study, no interim analyses or reports are planned. However, if critical safety information is obtained, the continuation of the trial will be reviewed.

#### 2.3.3 *Safety assessment and adverse events.*

The presence or absence of adverse events from the EP-01 body implantation site will be confirmed by CT and 3D data for slice thicknesses of 1 mm or less and 3–5 mm will be obtained. Acquired data will be submitted to the Safety Evaluation Committee. Scans will be conducted immediately after implantation, 1 day after implantation, 7 days after implantation, immediately before removal (however, if removal is performed before 7 days, the scan 7 days after implantation should be omitted), 1 day after removal, and 7 days after removal.

#### 2.3.4 *Adverse events.*

An adverse event will be deemed as any unfavorable sign, symptom, or illness (including abnormal changes in laboratory values) observed during the study examination and post-observation periods after use of the EP-01 (main unit and accessories) or other investigational device (EX-01 Extension Wire/EEG 1200 Series Neurofax Electroencephalograph). Adverse events are also defined to include abnormal fluctuations in clinical laboratory values observed during the investigational testing and post-observation periods after use of the EEG1200 Series Neurofax, regardless of the causal relationship to the investigational device. If an adverse event is observed, the investigator shall take appropriate measures. In addition, regardless of the presence or absence of a causal relationship with the investigational device, follow-up investigations shall be conducted until, in principle, the event normalizes or recovers to a level where it is no longer considered an adverse event. If an irreversible adverse event is observed due to an organic disorder, follow-up investigations should be conducted until the symptoms are stabilized or fixed. Symptoms within the range expected for the primary disease will not be treated as adverse events. If focal epilepsy resection is performed during the study period, symptoms resulting from this procedure will not be treated as an adverse event. The numbers of adverse events, adverse events attributable to the study device, serious adverse events, and serious adverse events attributable to the study device will be tabulated in terms of the number of occurrences, number of cases, and percentage of cases with adverse events.

Safety assessments will also involve the operation of the implanted device. In this study, “failure” is defined as any malfunction of the investigational device, adverse effect of the investigational device on the human body, damage, malfunction, or other general unwellness, whether due to manufacturing, delivery, storage, or use.

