**Methods and analysis:**

This multicenter, prospective, single-arm validation clinical trial is set to take place from March 2024 to August 2025, with follow-up extending to August 2026. The study will enroll 37 patients with refractory focal epilepsy across several Japanese medical institutions. Eligibility criteria include age 15–70 years and a vascular anatomy that allows the EP-01 to be guided into cerebral veins close to the epileptic focus. The EP-01 device will be inserted via the jugular veins, with electrodes positioned in target cerebral veins to record intracranial EEG data. The primary endpoint is the percentage agreement in lateralization diagnosis between EP-01 and conventional intracranial electrodes. Secondary endpoints include the diagnostic performance of EP-01, safety assessments, and seizure outcomes one year after resection surgery. Participants will undergo a screening period of 30 days, followed by the clinical trial period of up to two weeks, during which EP-01 will be inserted and monitored. A post-observation period of one week will follow device removal to assess potential adverse events. Data collection will involve EEG recordings, imaging studies, and safety evaluations, with results analyzed to determine the efficacy and safety of the device compared to traditional methods. This trial aims to provide critical data on the potential for EP-01 to serve as a less-invasive, effective alternative for diagnosing epileptic focus lateralization, potentially reducing the need for traditional invasive monitoring methods.

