### 1.3 Trial design

This multicenter, prospective, single-arm, validation clinical trial will be conducted on the study device from March 2024 to August 2025. The follow-up period for seizure evaluation will extend to August 2026. Evaluations of EP-01insertion performance will be determined by a Central Evaluation Committee comprising expert clinicians.

Essentially, the screening period is set at 30 days and the investigational testing period after insertion is a maximum of 2 weeks to facilitate testing and provide sufficient time for non-provoked spontaneous seizures to occur. The post-observation period (1 week) is judged as sufficient for monitoring potential adverse events associated with endovascular and intracranial implantation of electrodes. A summary of the processes for enrollment, conduct of the clinical trial, surgical treatment, and follow-up is shown in the Figure (Fig 1).

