**Secondary endpoints.**

(1)Diagnostic performance of the EP-01 alone, without reliance on intracranial electrodes, for the diagnosis of lateralization of the epileptic focus. To be obtained by third-party evaluation via the Central Evaluation Committee.(2)If there is a period during which only EP-01 is placed, comparative evaluation will be conducted between the EEG measurement performance with EP-01 alone and with both EP-01 and intracranial electrodes in place, to ensure that there is no mutual interference.(3)To determine whether the waveforms detected by EP-01 are brain-generated EEG components, EEG changes with eyes open and closed will be observed. Evaluation will be conducted by a third party appointed by the Central Review Committee.(4)In the case of intracranial electrodes placed bilaterally, the percentage of agreement on lateralization of the epileptic focus between EP-01 EEG with noninvasive findings and findings from bilateral intracranial electrode EEG with noninvasive findings will be compared.(5)In the case of intracranial electrodes placed bilaterally, the percentage of agreement on lateralization of the epileptic focus between EP-01 EEG without noninvasive findings and findings from bilateral intracranial electrode EEG without noninvasive findings will be compared.(6)Diagnostic performance for the lateralization of the epileptic focus by EP-01 (percentage agreement with the results of diagnosis by intracranial electrodes with noninvasive findings) with noninvasive findings as evaluated by the primary investigators.(7)Epilepsy surgery outcome will be evaluated by the International League Against Epilepsy (ILAE) seizure outcome classification 1 year after focal resection.(8)Success rate of EP-01 implantation, calculated as the number of EP-01s implanted immediately after implantation/ number of microcatheters implanted x 100. In addition, whether the EP-01 has migrated from the target vessel will be evaluated immediately before removal.(9)Safety evaluations:aSeverity and temporal characteristics of adverse events (including medical procedures for implantation and removal of EP-01) and adverse events judged from imaging studies, etc., attributable to the study device (e.g., hemorrhage, midline shift, CSF leakage) (Each Primary Investigator evaluate whether the adverse events are attributable to EP-01 or invasive electrodes and ultimately compare which device is responsible for the adverse events)bIncidence and timing of adverse events (period of occurrence: from the start of use of the study device to the end of the post-observation period, including the start of use of the study device and the end of the post-observation period)cAssociations with all study devices (EP-01 body and EP-01 accessories), medical procedures for EP-01 implantation and removal, and other devices used in the study, judged by extent, severity, treatment, and outcome(10)Other evaluations:aFailure of EP-01 (EP-01 itself and EP-01 accessories)bOther failures of investigational devices (EX-01 extension wire/electroencephalograph)

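### Symptoms attributed to resection are dropped before adverse events are counted, inside the week meant to detect harm after EP-01 removal, so symptoms of mixed cause can go untabulated

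*Protocol article*

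**What the plan says.** All references are to the protocol article.

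- **Definition.** Section 2.3.4 counts unfavourable findings in the examination and post-observation periods after use of the device. Its opening sentence sets no causal condition. The phrase "regardless of the causal relationship to the investigational device" also stands in that section, but in the sentence on laboratory values.
- **Exclusion.** The same section continues: "If focal epilepsy resection is performed during the study period", then "symptoms resulting from this procedure will not be treated as an adverse event". Symptoms expected from the primary disease are set aside in a similar way.
- **Window.** Item (9) of the secondary endpoints collects events "from the start of use of the study device to the end of the post-observation period". The abstract fixes the last part: "A post-observation period of one week will follow device removal to assess potential adverse events". Section 1.3 agrees: "The post-observation period (1 week) is judged as sufficient for monitoring potential adverse events". It goes on to tie those events to endovascular and intracranial electrode implantation.
- **Overlap.** Section 2.1.3 provides for a resection inside that window ("If focal resection surgery is performed before the end of the post-observation period") and adds that "concomitant medications and concomitant therapies used for these procedures are also excluded from recording".
- **Attribution and review.** Item (9) asks each site's principal investigator to attribute adverse events to EP-01 or to the invasive electrodes. Section 2.3.1 has a three-specialist safety committee evaluate device-related adverse events. Section 2.3.3 sends CT data, including scans 1 and 7 days after removal, to that committee.

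**The concern.** A causal judgement is made at the point where the plan decides whether something is an adverse event at all. Normally an event is recorded first and its cause judged afterwards, so that a doubtful judgement stays visible. Here a symptom judged to be surgical leaves the data set that feeds the safety tables.

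This matters because safety is a stated objective, and the post-observation week is the only period the article plans for detecting new adverse events after EP-01 is removed. The one-year follow-up in section 2.2.3 concerns seizure outcome. If brain surgery falls in that week, a new deficit or other symptom may have several plausible causes, and the printed rule gives the benefit of the doubt no visible place.

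**Working it through.** The plan states no safety rate or threshold, so there is no figure of its own to reproduce. The point rests on reading the sections together, with a small illustration of scale.

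**Step 1: can a resection fall inside the safety window?** Yes. The window ends one week after removal (abstract; section 1.3; secondary endpoint 9), and section 2.1.3 makes explicit provision for a resection before that end. The overlap is stated, not inferred.

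**Step 2: what happens to a symptom classed as resulting from the resection?** Section 2.3.4 plans four tabulations: all adverse events, those attributable to the study device, serious adverse events, and serious adverse events attributable to the study device. A symptom that is not an adverse event enters none of them, not even the all-cause count.

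**Step 3: is there a later step that could bring it back?**
- Attribution under secondary endpoint 9 applies to adverse events and offers EP-01 or invasive electrodes. Resection is not among the options, and an excluded symptom does not get that far.
- The committee in section 2.3.1 evaluates device-related adverse events. No printed step sends it symptoms already classed as surgical.
- CT under section 2.3.3 goes to the Safety Evaluation Committee however the site classifies a symptom. This is a real safeguard for findings that imaging can show.
- Antithrombotic therapy is documented to the end of post-observation (section 2.1.3), which leaves some trace of a treated thrombosis. Other drugs and therapies used for the resection are not recorded.

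The remaining gap is mainly clinical symptoms that both a device and the resection could explain.

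**Step 4: direction.** The exclusion removes events and adds none. Where a symptom of mixed or unclear cause is classed as surgical, the reported rate can only fall.

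**Step 5: scale, as illustration only.** Input: N = 37, the enrolment target in section 2.1.6. Assumption: all 37 are in the safety denominator. One event is 1/37 = 2.7 percentage points. Exact (Clopper–Pearson) 95% upper limits are the 0.975 quantile of Beta(x + 1, 37 − x); for x = 0 this is 1 − 0.025^(1/37).

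| Events | Rate | Upper limit |
|---|---|---|
| 0/37 | 0% | 9.5% |
| 1/37 | 2.7% | 14.2% |
| 2/37 | 5.4% | 18.2% |

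Any one or two uncounted events would shift the limits in this way. The table does not estimate how many are lost under this rule: that needs the number of early resections and the rate of misattribution, and the article gives neither.

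**The case against.** The strongest reply has four parts.

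1. **The rule is narrow.** It sets aside only symptoms that result from the resection, not everything that follows it. Device harm is lost only if a symptom is misattributed or has a mixed cause. This stands, and it limits the point to such symptoms.
2. **Imaging is reviewed independently.** Scans before removal and on days 1 and 7 after it go to the committee, and secondary endpoint 9 names haemorrhage, midline shift and CSF leakage as findings of interest. This also stands for visible harm, although no printed rule says how a finding on a scan taken after resection is to be counted.
3. **Setting apart the sequelae of a separate operation is a deliberate choice**, and section 1.3 aims the window at implantation harm. Separating them is reasonable. Doing so before counting is the weakness, since a separate row would serve the same aim without losing information.
4. **The full protocol and case report form are not shown** and may hold rules on recording and adjudication. That is so. But the point concerns an exclusion that is printed, not a missing detail.

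A reader might infer that late EP-01 harm disappears from the record and that no later review could find it. The article does not support that. It says such symptoms are not treated as adverse events; it does not say they go unrecorded in source documents. Only drugs and therapies are expressly left unrecorded, and the CT route does not depend on the site's classification. Nor should the phrase about causal relationship be read as a general all-cause rule, since it belongs to the laboratory sentence. The all-cause reading rests on the opening definition.

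**Conclusion.** The concern holds in limited form. Section 2.3.4 applies a causal filter before counting, and section 2.1.3 shows that the filter can operate inside the only post-removal safety window. A clinical symptom of mixed or unclear cause can therefore be absent from all four tabulations and from device attribution, with a downward effect on the reported rate.

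The size of the effect cannot be computed from the article; 2.7 points per event at N = 37 shows only how much a single event weighs. The conclusion assumes that some patients are resected within the window and that some symptoms there cannot be cleanly assigned to one cause. It does not touch the primary endpoint, the sample size or the error rate. It should be corrected because safety is one of the trial's two aims and the correction is cheap.

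**What to change.** Amend section 2.3.4 in three respects:

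1. Record every event through the end of post-observation, including events after a resection, with a judged-cause field: EP-01, intracranial electrodes, resection, primary disease, or unclear.
2. Have the existing Safety Evaluation Committee review post-resection events that the site classes as surgical or unclear. The field alone would not be enough: an event that the site calls surgical would move to another row and leave the device-attributable count unchanged.
3. Tabulate resection-attributed events in a separate row, and show totals with and without them.

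The cost is one case report form field and one table row. The downside is that more post-surgical events must be recorded, with some added review for a committee that already exists. Sample size, primary analysis and patient care do not change.
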